### Power and sample size

The average English school has approximately 190 students per year, although this varies across schools. A systematic review of school-based secondary preventive interventions to prevent violence [69] reported a pooled effect size of 0.41 on measures of aggressive behaviour. Effect sizes for aggressive behaviour from similar interventions approximate 0.3 to 0.4 SDs in males. Recent data from three large UK school cohorts [70] suggest that intra-cluster correlation coefficients (ICC) for aggression and bullying outcomes vary between 0.01 and 0.03

We propose to recruit sufficient participants to detect a difference between groups of 0.25 SD with 90% power and a 5% level of significance. This is considered to represent a moderate size of effect and in line with the effect sizes seen in the literature.

Conservatively, taking an ICC of 0.04 and 150 students per school, a trial involving 20 schools per arm will provide 90% power to identify an effect size of 0.25 SD with a 5% significance level. If two schools per arm (that is 10%) were to be lost to follow-up over the course of the trial, we would still have 80% power to detect an effect size of 0.25 SD.

The total student sample size will be approximately 6,000. As we will be surveying all young people in the relevant school year at each follow-up, this sample is likely to remain similar across the study.

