**Methods:**

Design: cluster randomised trial.

Participants: 40 state-supported secondary schools. Outcomes assessed among the cohort of students in year 8 (n = approximately 6,000) in intervention year 1.

Intervention: INCLUSIVE is a school-led intervention which combines changes to the school environment with the promotion of social and emotional skills and restorative practices through: the formation of a school action group involving students and staff supported by an external facilitator to review local data on needs, determine priorities, and develop and implement an action plan for revising relevant school policies/rules and other actions to improve relationships at school and reduce aggression; staff training in restorative practices; and a new social and emotional skills curriculum. The intervention will be delivered by schools supported in the first two years by educational facilitators independent of the research team, with a third locally facilitated intervention year.

Comparator: normal practice.

Outcomes: primary: 2 primary outcomes at student level assessed at baseline and at 36 months:
Aggressive behaviours in school: Edinburgh Study of Youth Transitions and Crime school misbehaviour subscale (ESYTC)Bullying and victimisation: Gatehouse Bullying Scale (GBS)

Secondary outcomes assessed at baseline, 24 and 36 months will include measures relating to the economic evaluation, psychosocial outcomes in students and staff and school-level truancy and exclusion rates.

Sample size: 20 schools per arm will provide 90% power to identify an effect size of 0.25 SD with a 5% significance level.

Randomisation: eligible consenting schools will be randomised stratified for single sex versus mixed sex schools, school-level deprivation and measures of school attainment.

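### The stated power of 90% with 20 schools per arm and 80% with 18 does not follow from the stated inputs, and the two figures do not fit each other; both err on the conservative side.

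*Protocol article*

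**What the plan says.** The Power and sample size section of the protocol article sets the target as enough participants to "detect a difference between groups of 0.25 SD" with "90% power and a 5% level of significance". It then gives its working assumptions, "taking an ICC of 0.04 and 150 students per school", and the result: "a trial involving 20 schools per arm will provide 90% power to identify an effect size of 0.25 SD with a 5% significance level". The Methods paragraph of the abstract repeats that result: "20 schools per arm will provide 90% power to identify an effect size of 0.25 SD with a 5% significance level".

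The next sentence covers the loss of whole schools. If two schools per arm, which the article equates to 10%, "were to be lost to follow-up over the course of the trial, we would still have 80% power" for the same 0.25 SD. No input other than the number of schools is changed for this scenario, and neither figure is presented as a minimum. The Randomisation section gives 1:1 allocation. The article does not say whether the 5% level is one-sided or two-sided. It notes that the size of a school year differs between schools, but gives no coefficient of variation.

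**The concern.** A drop from 90% to 80% is large for the loss of one school in ten. When only the number of equal-sized clusters changes, the information about the treatment effect falls in the same proportion, here to 90% of its planned value. Starting from 90% power, that should cost a few points, not ten. This suggests that at least one figure is wrong, or that the two were worked out under different assumptions.

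The sentence is the article's only quantified statement of how much school loss the trial can bear. As printed, it tells the reader that two lost schools per arm bring the trial down to the conventional 80%. If that is not what the inputs imply, the trial's robustness is misdescribed, and nobody can reproduce the sample size from the section that justifies it.

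**Working it through.** **Inputs**
- From Power and sample size: difference d = 0.25 SD (SD = 1), alpha = 0.05, ICC = 0.04, m = 150 students per school, k = 20 schools per arm, or 18 after the loss.
- From Randomisation: 1:1 allocation.
- Assumed: two-sided test, equal school sizes.

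**Formulas**
- Design effect: DE = 1 + (m − 1) × ICC = 1 + 149 × 0.04 = 6.96.
- Standard error of the difference: SE = sqrt(2 × DE / (k × m)).
- Noncentrality: d / SE.
- Power: Φ(noncentrality − 1.960) by normal approximation, or noncentral t with 2k − 2 degrees of freedom.

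**Step 1: the stated 90% at 20 per arm**
- SE = sqrt(2 × 6.96 / 3000) = 0.0681; noncentrality = 3.670.
- Normal: Φ(1.710) = 95.6%. Noncentral t, 38 df: 94.7%.
- The 90% is not reproduced.

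**Step 2: the stated 80% at 18 per arm**
- SE = sqrt(2 × 6.96 / 2700) = 0.0718; noncentrality = 3.482.
- Normal: Φ(1.522) = 93.6%. Noncentral t, 34 df: 92.2%. Removing a further 7 df for the strata gives 91.9%.
- The 80% is too low by 12 to 14 points.
- A one-sided 5% test widens the gap (97.9% at 20 per arm and 96.7% at 18, normal).
- On these inputs power comes down to about 81% only at 13 schools per arm (81.0%, t) or 12 (81.1%, normal).

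**Step 3: do the two figures fit each other?**

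This step does not depend on the ICC, school size or SD. Suppose power at 20 per arm is exactly 90%.
- Noncentrality at 20 = 1.960 + 1.282 = 3.242.
- At 18 it is 3.242 × sqrt(18/20) = 3.075.
- Power at 18 = Φ(3.075 − 1.960) = 86.8% (normal); the t version gives 86.6%.

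To fall from 90% to 80%, information must drop to ((1.960 + 0.842) / 3.242)² = 74.7% of plan. That leaves 0.747 × 20 = 14.9 schools per arm, a loss of about five, not two.

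**Step 4: could an unstated allowance explain the pair?**

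For unequal school sizes the design effect is 1 + ((1 + CV²) × m − 1) × ICC. With CV = 0.5 it is 1 + (1.25 × 150 − 1) × 0.04 = 8.46.

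| Allowance (noncentral t) | 20 per arm | 18 per arm |
|---|---|---|
| ICC 0.05 | 90.1% | 86.6% |
| School-size CV 0.5 | 90.0% | 86.6% |
| School-size CV 0.6 | 87.8% | 84.0% |
| Alpha 0.025 | 90.4% | 86.7% |
| ICC 0.061 (chosen to give 80% at 18) | about 84% | about 80% |

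Several plausible allowances bring 20 per arm to 90%. None of them gives 80% at 18, and the ICC that gives 80% at 18 leaves only about 84% at 20.

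**The case against.** The strongest reply is that both figures err on the safe side. 90% and 80% are conventional thresholds, and the wording about still having 80% can be taken as a floor. Read that way, both statements are true together on the printed inputs: 94.7% exceeds 90%, and 92.2% exceeds 80%. The Trial status section adds that all schools had been recruited at submission, so no recruitment decision turns on the figure. The point about direction and consequence stands, and it limits the severity. The floor reading is weaker, because the text does not present either figure as a minimum. A floor 12 points below the computed value also says little about tolerance to school loss.

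A second reply is that 95% and 92% are themselves optimistic, since they assume equal school sizes while the article acknowledges that year size differs. This also stands. It is why the correction should not print those figures without their assumption.

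A reader might infer three stronger things that the article does not support:
- **The trial is underpowered or the design must change.** The error runs the other way.
- **The oversight committees will act on 80% as a threshold for school withdrawal.** The Data Monitoring Committee section gives that committee data quality, completeness and potential harms. The Risks section has the Trial Steering Committee decide on major harms. Neither contains a power-based rule.
- **The misstatement conceals spare power that could pay for a multiplicity adjustment over two primary outcomes.** The surplus depends on equal school sizes. A CV of 0.5 removes it, and the article gives no CV, so no surplus is established.

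**Conclusion.** The point holds as a correction to the text. On the stated inputs, with a two-sided 5% test and equal school sizes assumed, power is about 95% at 20 schools per arm, not 90%, and about 92% to 94% at 18, not 80%. If the 90% rests on an allowance the article does not name, the matching figure after losing two schools per arm is about 87%. That last result needs only that the number of schools is the sole thing that changes, which is how the sentence is written. The adequacy of 20 schools per arm is not in doubt on the printed inputs. What is wrong is the stated tolerance to school loss and the reproducibility of the calculation.

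**What to change.** Recalculate the two power figures together under one set of assumptions and restate them in Power and sample size, naming the sidedness of the test and the method. There are two acceptable forms:

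- **On the printed inputs:** state that, with ICC 0.04, 150 students in every school and a two-sided 5% test, 20 schools per arm give about 95% power for 0.25 SD, and 18 per arm give about 92% (noncentral t).
- **With an allowance:** name it and give the pair that goes with it. For a school-size CV of 0.5, used here only as an illustration, that is about 90% and 87% (noncentral t).

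The second form is preferable if the 90% was meant to absorb unequal school sizes, because it keeps the headline figure and replaces only the 80%. If the 90% changes, change it in the abstract too. The cost is a sentence or two of text and one short recalculation, with no change to the design, the number of schools or the analysis.

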### Economic evaluation

The aim of the economic evaluation is to assess the costs, consequences and cost-effectiveness of the INCLUSIVE intervention compared with standard school-based practices for managing aggression.

The primary economic evaluation will take the form of a within-trial cost-consequence analysis, with a secondary analysis that will report relative cost-utility with health outcomes expressed in terms of Quality-Adjusted Life-Years (QALYs), as recommended by the National Institute for Health and Care Excellence (NICE)’s public health methods guidance.

This NICE guidance also recommends that the base-case cost-effectiveness estimate is presented from a public sector perspective as this allows the costs and benefits of more than one central/local government body to be taken into account. This statement is particularly pertinent to INCLUSIVE as the costs of implementing it are likely to fall on the educational sector, yet there are potential cost implications for sectors such as the NHS, the police and the judiciary through reduced anti-social behaviour.

The costs to the education sector include cost of the facilitator to deliver the intervention and the cost of staff time. The facilitator costs for the delivery of the intervention will be collected using log sheets. The impact on staff time for training and delivering bullying policy will be obtained as part of the process evaluation. It is possible that the intervention might offset some of the staff time related to dealing with pupil aggression or bullying behaviour and this will be captured as part of the teacher survey. It might also impact on teacher health and we will capture this by valuing the number of days off work, which will be captured as a secondary outcome measure. The implications for NHS resource use and policing will be identified with specific questions in the student survey and valued accordingly. The time horizon will capture costs and outcomes within the trial.

Changes in health-related QoL (as expressed using QALYs) will be measured from the study participants’ (that is student’s/teacher’s) perspective.

The *Child Health Utility* (*CHU*) *9D measure* (CHU-9D) [71] will be used to assess student’s health-related QoL as part of the economic evaluation. The CHU-9D is a validated age-appropriate measure that was explicitly developed using children’s input and has been suggested to be more appropriate and function better than other health utility measures for children and adolescents. For teachers, we will use the SF-12 for this purpose [67]. Student and teacher utility values will be collected (at baseline and at follow-up surveys at 24 and 36 months) using the CHU-9D and by converting the SF-12 questionnaires respectively.

### Process evaluation

Data will be used to examine intervention implementation and receipt and examine possible causal pathways in order to facilitate interpretation of outcome data. In line with Medical Research Council (MRC) guidance on complex interventions, this component of the trial will also enable refinement of the intervention logic model. Informed by existing frameworks, the process evaluation will examine the following:

#### Trial context

We will assess the context within the intervention and control arms, including what other relevant services and practices operate, such as the nature of school discipline systems, staff training, social skills curricula and student participation in decision-making. This will draw on annual: interviews with intervention facilitators (n = 5); telephone interviews with action-team members (n = 2 per school) in intervention schools; interviews with the Senior Leadership Team (SLT) (n = 1 per school) and other staff (n = 2 per school) in intervention and control schools; and 2 focus group discussions (FGDs) with students and one FGD with staff in 8 randomly selected intervention and control schools (purposively sampled by students participation, gender and age and staff participation and role), which will also allow us to explore mechanisms of actions.

#### Trial arm fidelity

We will assess the fidelity with which INCLUSIVE is delivered in each school. In addition to the above sources, we will draw on: annual structured quantitative researcher observational data of a random selection from each school of one action team meeting (n = 20), staff training (n = 20) and one curriculum session (n = 20); structured diaries of action team meetings and staff training maintained by intervention facilitators in each school; qualitative data from action-team minutes (from 10 randomly selected schools in the full trial). We will assess fidelity and acceptability rates for each facilitator.

#### Participation, reach and dose

We will assess the extent to which students and staff are involved in or in receipt of intervention processes and outputs. This will draw on quantitative data from 24- and 36-month follow-up surveys of students, staff and action group members. The last of these will also assess the extent to which members felt empowered to participate in decision-making using a modified version of the Learner Empowerment Scale [72].

#### Reception and responsiveness

We will assess the *experiences* of participation in INCLUSIVE and in school environments shaped by this, to assess *acceptability and any barriers or facilitators to this*. This will draw on the annual interviews with action-team members (n = 2 per school) in intervention schools; interviews with SLT (n = 2 per school) and other staff (n = 2 per school) in intervention and control schools; and FGDs with students in 8 randomly selected intervention schools described above.

#### Intermediate outcomes

To assess possible intervention causal pathways and examine whether these mediate intervention effects in order to assess and refine our logic model, we will use two measures that examine students’ perception of the school environment and their connection to the school:Beyond Blue School Climate Questionnaire (BBSCQ) [73] which will be used to measure students’ perceptions of the school climate. It consists of twenty-eight items which produce an overall score and also assesses four key domains of school climate (subscale): supportive teacher relationships, sense of belonging, participative school environment, and student commitment to academic values.Student reports of anti-school actions will be assessed using the ESYTC Self-Reported Delinquency (SRD) subscale. Involvement with anti-school peer groups will be assessed using a single item measure previously used in the YPDP evaluation measure.

### Analyses

#### Outcome analyses

All primary analyses will be carried out according to the principle of intention-to-treat (ITT) and using multilevel modelling to take into account clustering at the school level. The primary analysis will be a repeat cross-sectional analysis that includes data from all students at both time points for two main reasons: (1) the intervention is a whole school intervention and, based on a school-level theory of change, is expected to impact on all pupils, not just on those pupils who were present at baseline; (2) the literature suggests that in cluster randomised trials, when migration into or out of the clusters is high over time, the baseline cohort may not remain representative of the cluster and therefore repeated cross-sectional analysis is preferred to minimise bias. Based on our pilot data and existing research on student mobility, we anticipate student turn-over of up to 25% in some schools over 36 months. Because of this we will use multilevel analyses that include all students at all time-points, which essentially provides a repeat cross-sectional analysis with a nested longitudinal cohort.

Data will be analysed by appropriate multivariate regression models, fitting pre-hypothesised potential confounders as covariates. Note that data on ethnicity and socio-economic status will be collected by self-report from students. Both primary outcomes will be fully analysed and reported separately, using separate multi-level models. A small number of secondary analyses based on explicit hypotheses, for example, subgroup effects/causal pathway analyses will be specified in advance. These secondary analyses will include a longitudinal analysis of pupils present at both baseline and follow-up, with further analyses using individual-level baseline data to explore the implications of missing individual-level outcome data.

Secondary analyses will include staff outcomes and will be carried out according to the principle of ITT using the same approach to modelling as described for the student outcomes. Secondary analyses will also examine moderators and mediators. We will examine whether intervention effects are moderated by individual-level gender and socio-economic status measured using the Health Behaviours in School-aged Children (HBSC) Family Affluence Scale [74] and sex, as well as by school-level stratifying factors (single sex versus mixed sex school; school-level deprivation; value added strata); and facilitator, though these analyses may be underpowered. We will examine whether intervention effects are mediated by process and intermediate outcome measures. Other such analyses will be informed by hypotheses derived from analysis of qualitative data.

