### Randomisation

Eligible schools whose head-teacher gives informed written consent to participate will be allocated with a 1:1 ratio between intervention and control arms. Stratified randomisation will be undertaken remotely by the Clinical Trials Unit (CTU) at the London School of Hygiene & Tropical Medicine (LSHTM). To promote baseline equivalence, we will stratify by key school-level determinants of violence:Single sex versus mixed sex school.School-level deprivation, as measured by percentage of students eligible for free school meals (low/moderate 0 to 23%; high >23%, with 23% being the median for England).School ‘best eight value added’ in GCSE exams (above and below median for England of 1,000). Value added (VA) score is a school-level measure of students’ attainment in public exams adjusting for their attainment on entry to the school. We use VA rather than Ofsted ratings for schools as there is better evidence for VA being associated with violence rates [59].

Schools will be allocated randomly within each of these eight strata.

Protecting against selection bias:School level: the randomisation schedule will be drawn up once the schools have consented and after the baseline survey, thus guarding against selection biases at entry of clusters to the trial. The randomisation may occur sequentially in groups of 10 schools, should there be any delays with baseline surveys in some schools. As with most social intervention trials, schools, their students, teachers and other staff cannot be ‘blinded’ to allocation status. However, fieldwork staff will be blinded to allocation as will data-input staff. Analysis of follow-up quantitative data will be undertaken blind to allocation.

Retention of control schools will be maximised by ensuring regular senior liaison and provision of participation incentives (£500 per school).(2)Student level: we had very high student participation in our pilot study: 96% of eligible at baseline and 93% at follow-up. To minimise bias, we will use in-school, mail and telephone contacts to try to include all enrolled students absent at either baseline or follow-up questionnaires. Note we will not attempt to follow-up students who have left the school.A flow chart of recruitment and intervention and control treatment is shown in Figure 1.

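### The primary 36-month comparison is not said to adjust for baseline; adding each school's baseline mean would gain precision without dropping any student

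*Protocol article*

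**What the plan says.** Under Outcome analyses the article fixes the type of primary analysis: "The primary analysis will be a repeat cross-sectional analysis that includes data from all students at both time points". Two reasons follow. The intervention acts on the whole school, so all pupils should count; and when migration is high the baseline cohort may stop representing the school, with turnover of up to 25% expected in some schools over 36 months. The section adds that the multilevel models take in all students at all time-points, so that a longitudinal cohort sits inside the repeated cross-sections. Covariates are described only as potential confounders hypothesised in advance; the baseline outcome is not named.

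Students' own baseline data appear one step down: "These secondary analyses will include a longitudinal analysis of pupils present at both baseline and follow-up, with further analyses using individual-level baseline data". The purpose given for those further analyses is to explore missing outcomes.

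Two other sections matter. The Abstract says both primary outcomes are assessed at baseline and 36 months. Randomisation says the schedule is drawn up after the baseline survey, so baseline scores are pre-randomisation covariates in every school.

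**The concern.** The article treats the choice as one between a closed cohort and a repeated cross-section. A third option is not mentioned: analyse everyone present at 36 months and adjust for the baseline level of the outcome. Both stated reasons argue against restricting the analysis to students seen at baseline. Neither argues against adjustment, because a student who joins later still belongs to a school with a baseline mean.

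The form of the contrast matters because there are only 40 schools and most of the noise lies between them. A change-by-arm contrast with separate baseline means subtracts chance baseline differences in full. When the two waves, three years apart, correlate only moderately, that can be less precise than ignoring baseline. An analysis plan could follow the article's wording and arrive at that contrast.

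**Working it through.** **Inputs from the article.** Power and sample size: "Conservatively, taking an ICC of 0.04 and 150 students per school", 20 schools per arm, effect 0.25 SD, 5% significance (taken as two-sided). Randomisation: schools "will be allocated with a 1:1 ratio between intervention and control arms".

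**Inputs assumed, not in the article.** Correlation between a school's true baseline and 36-month level, rc = 0.3, 0.5 or 0.7. Correlation of a student's own two scores within school, 0.4. Share of 36-month respondents with their own baseline, 80%.

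**The plan's own figure.** The article says "a trial involving 20 schools per arm will provide 90% power". The design effect is 1 + 149 × 0.04 = 6.96, so the effective number per arm is 20 × 150 / 6.96 = 431. Power is 95.6% (normal) or 94.7% (t, 38 df), higher than the 90% stated. With 18 schools per arm it is 93.6% or 92.2%, against 80% stated. Both stated figures err low, and the calculation takes no credit for baseline data.

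**Variance of one school's contribution (total variance 1).** The between-school part is 0.04 and the within-school part is 0.96/150 = 0.0064. The between-school share is 0.04/0.0464 = 86%.

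- Follow-up only: 0.04 + 0.0064 = 0.0464.
- Change by arm: 2 × [(1 − rc) × 0.04 + (1 − 0.8 × 0.4) × 0.0064] = 0.0647 / 0.0487 / 0.0327.
- Conditioned on school level and own score: (1 − rc²) × 0.04 + (1 − 0.8 × 0.4²) × 0.0064 = 0.0420 / 0.0356 / 0.0260.
- Adjusted for the observed school baseline mean only: the covariance of the two school means is rc × 0.04 + 0.8 × 0.4 × 0.0064 = 0.0140 / 0.0220 / 0.0300. Dividing by 0.0464 gives r = 0.303 / 0.475 / 0.648, and 0.0464 × (1 − r²) = 0.0421 / 0.0359 / 0.0269.

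**Standard error and power.** SE = √(2 × variance / 20); power at 0.25 SD from the noncentral t with 38 df.

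| Analysis | SE at rc 0.3 / 0.5 / 0.7 | Power (%) |
|---|---|---|
| Follow-up only | 0.068 (any rc) | 95 |
| Change by arm | 0.080 / 0.070 / 0.057 | 86 / 94 / 99 |
| School level and own score | 0.065 / 0.060 / 0.051 | 96 / 98 / 99.8 |
| School baseline mean only | 0.065 / 0.060 / 0.052 | 96 / 98 / 99.7 |

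Full conditioning cuts the variance by 35 / 27 / 21% against change by arm (for example 1 − 0.0420/0.0647 = 35%) and by 9 / 23 / 44% against follow-up only. The school mean alone comes close: 35 / 26 / 18% and 9 / 23 / 42%.

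**Cross-check by another method.** Generalised least squares for a two-wave cluster design, with 25% turnover and student correlation 0.4, gives SEs of 0.081 against 0.065 at rc = 0.3, 0.070 against 0.060 at 0.5, and 0.050 against 0.046 at 0.8. The first of each pair is an unlinked arm-by-time contrast; the second links students and fits a common baseline mean. For rc from 0.3 to 0.95, student correlation from 0.2 to 0.6 and turnover from 0 to 25%, the variance reduction is about 5% to 36%. If a common baseline mean is already fitted, linking students' own scores removes only a further 0% to 9%.

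**The case against.** The strongest reply is that the article never states a change-by-arm contrast. It describes multilevel models that include everyone at both waves, and its remark about a cohort nested in the cross-sections leaves room for linking students. The listed secondary use of individual baseline data has one stated purpose and does not rule out others, and the covariate wording does not exclude a baseline score. A journal article normally leaves the exact model to the analysis plan. This stands to the extent that a reader might infer the plan discards baseline information or commits to the inefficient contrast, and the text supports neither inference. It does not dispose of the point: the article names and justifies the type of primary analysis, and its reasons do not bear on adjustment.

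A second reply is that power is adequate in most scenarios. This also stands. Follow-up only gives 95%, and under change by arm power falls below 90% only at the lowest assumed correlation.

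A third reply concerns the remedy. A reader might infer that using every student's own baseline score, with an indicator for joiners, is free of cost because baseline precedes randomisation. It is not. Joiner status arises after randomisation, in a trial where exclusion is an outcome and the intervention changes discipline policy. A linked two-wave model is not strictly equivalent either: leavers' baselines enter it although leavers are not followed up, so it no longer targets only the students present at 36 months. Neither difficulty applies to the school's baseline mean, which is fixed before allocation and defined for every student.

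**Conclusion.** The point holds as one of efficiency. The article does not say that the primary comparison conditions on the pre-randomisation outcome, and its reasons for the repeat cross-section do not argue against doing so. Against a change-by-arm contrast with separate baseline means, conditioning lowers the SE from about 0.080/0.070/0.057 to 0.065/0.060/0.051 at assumed school-level correlations of 0.3/0.5/0.7. Against follow-up only (0.068), the gain is small at 0.3 and substantial at 0.7. The size rests on correlations the article does not give and on a contrast it does not state; if the intended model already links students or shares a baseline mean, part or most of the gain is already there. The documents do not support reading this as a bias, as an error in the estimand, or as evidence that the trial is underpowered. The change is worth making because it needs no new data and costs almost nothing.

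**What to change.** Keep all students surveyed at 36 months in the primary analysis. State in Outcome analyses that the primary GBS and ESYTC models at 36 months adjust for the school's baseline mean of the same scale. Do not put a no-baseline indicator for joiners in the primary model. Keep models that use students' own baseline scores, and the unadjusted repeat cross-section, as sensitivity analyses.

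The cost is one sentence and one school-level degree of freedom (37 instead of 38). There are no new data, no students are lost, and the target population and intention-to-treat principle are unchanged.
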